## **7. METHODOLOGY**

### *7.1 Definition of Baseline and Endline Cohorts of HIV-Infected Pregnant Women*

We will retrospectively abstract data from routinely collected information in CHW logs and facility registries of patient medical information (see **Figure 1** for an overview of the impact and process outcomes). The research team will collect data from two 6-month cohorts (baseline and endline) of women who are 90 days postpartum to ensure that we can measure retention in care and adherence at 90 days postpartum (**Figure 4**):

- The baseline cohort will include HIV-infected women who were 90 days postpartum between July 1 and December 31, 2014; this corresponds to infants born between April 1 and September 30, 2014. These women are unexposed to the intervention.
- The endline cohort will include HIV-infected women who are 90 days postpartum between May 1 and October 31, 2015, corresponding to infants born between February 1 and July 31, 2015. These women will have been exposed to the intervention during the last 4-9 months of their pregnancy and during their entire 0-90 day postpartum period. This is a reasonable amount of exposure to the intervention given that, on average, women in Tanzania are 5.4 months pregnant at their first ANC visit when they have the initial opportunity to initiate ART.

**FIGURE 4.** Cohorts for Baseline and Endline Data Collection

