### 6.3 Evaluation Design

The impact evaluation will evaluate the effect of integrating community-based MNCH and PMTCT services using CHWs in Shinyanga, Tanzania. Using a cluster randomized design, we will allocate 30 villages to the treatment or comparison condition and measure the community-level outcomes at baseline (0 months) and endline (9 months) using routinely collected data from CHWs and health facilities. We will determine the impact of the intervention on the primary outcomes of ART initiation, retention in care, and adherence to ART (**Evaluation Question #1**). We will determine whether the effect of the intervention is stronger among women who received more visits from CHWs (**Evaluation Question #2**). Lastly, we will conduct a mixed methods process evaluation with the primary stakeholders, including but not limited to CHWs, clinic staff, and pregnant and postpartum women, to assess the intervention's: 1) acceptability; 2) feasibility; and 3) potential spillover benefits on other outcomes (**Evaluation Question #3**). If the data from the evaluation supports scale-up of the integrated strategy, we will use these data to refine the intervention protocols for wider adoption within Tanzania and elsewhere.

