### 6.4 Sample Size and Power

In health facilities where there are  $< 50$  HIV-infected pregnant or postpartum women in the baseline or endline cohorts (determined with the ANC register), we will abstract data from the ART register on all women. At health facilities where there are  $\geq 50$  HIV-infected pregnant or postpartum women in the cohorts, we will abstract a predetermined sampling fraction such that 75% of women are sampled from cohorts with 50-100 women, 50% of women are sampled from cohorts with 100-200 women, etc. This approach will ensure that the sample size is adequate to detect a minimum increase in retention in care at 90 days postpartum.

We have powered the study for the outcome of retention in care 90 days postpartum. In our aforementioned preliminary analysis of pregnant women in Shinyanga, we found that more than

36% of HIV-infected pregnant women who initiated ART were lost within 100 days. Thus, we will conservatively assume that in the comparison communities, 67% of women will be retained in care at 90 days postpartum. For logistical and budgetary reasons, especially given the rapid nature of the impact evaluation, we have determined that we can reasonably study 15 intervention communities (a total of 30 CHW, 2 per village, and 15 RCH facilities) and 15 comparison communities.

If we assume an ICC of 0.05 and that the intervention will increase the proportion of women who are retained in care 90 days postpartum from 67% to 80% (detectable effect size of 13 percentage points, or 20%), we will require at least 36 observations per community, or 537 observations from the intervention and comparison groups, to have 80% power to reject the null hypothesis of no effect. Obtaining data from at least 36 HIV-infected women per facility is well within the normal volume of clients at RCH clinics, as many RCH clinics initiate an average of 11 HIV-infected women on ART/ARVs per month. With at least 6 intervention months in each community, we will ensure that we can easily meet this goal.

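### Section 7.1 contradicts itself: no launch date can leave the whole baseline cohort unexposed and also give every endline woman at least 4 months of exposure in pregnancy

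*Protocol*

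**What the plan says.** Section 7.1 of the Protocol defines two six-month cohorts by calendar date.

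- **Baseline:** "HIV-infected women who were 90 days postpartum between July 1 and December 31, 2014". The matching births are those of 1 April to 30 September 2014. Of this cohort it says "These women are unexposed to the intervention", with no limit to pregnancy.
- **Endline:** "90 days postpartum between May 1 and October 31, 2015, corresponding to infants born between February 1 and July 31, 2015". Of this cohort it says "These women will have been exposed to the intervention during the last 4-9 months of their pregnancy", and it adds the full first 90 days after delivery.

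The readable text gives no launch date. Section 6.3 places baseline at 0 months and endline at 9 months. Section 6.4 says "With at least 6 intervention months in each community". Section 7.4 analyses all three impact outcomes by difference-in-differences, so the baseline cohort enters each main estimate.

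**The concern.** The two exposure statements place the launch on different sides of the last quarter of 2014. The endline statement needs it at or before the start of that quarter, the baseline statement after its end.

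This matters because the intervention does not stop at delivery. Under Section 5, community health workers hand the card to postpartum as well as pregnant women, trace women who miss appointments from the ART register, and counsel on adherence at monthly home visits. Section 6.2 measures retention as attendance between 60 and 90 days postpartum, and adherence at 90 days. A baseline woman in an intervention community who is still within 90 days of delivery at launch can therefore be exposed before her outcome is recorded. Any benefit to her raises the intervention arm's baseline, and difference-in-differences subtracts it.

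If the launch was instead after December 2014, the baseline is clean. The endline cohort then had much less pregnancy exposure than stated, and the ART-timing outcome is the one that suffers.

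**Working it through.** **Inputs.** Baseline births 1 April-30 September 2014 (183 dates) and endline births 1 February-31 July 2015 (181 dates), Section 7.1. Retention window 60-90 days, Section 6.2. Mean stage of pregnancy at first antenatal visit 5.4 months, Section 7.1. The launch date is unknown, so a range is tested. Births are assumed uniform over each window; a month is 30.44 days.

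**The plan's own range.** Pregnancy exposure = the smaller of (birth date − launch date) and the length of pregnancy. With launch on 1 October 2014, a birth on 1 February 2015 has 123 days, or 4.04 months. The latest births have a full pregnancy, 8.7-9.2 months for 266-280 days. The stated 4-9 months thus reproduces with a launch at about 1 October 2014.

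**The baseline statement.** 30 September 2014 + 90 days = 29 December 2014, and the stated assessment window closes on 31 December. For every baseline woman to be unexposed up to day 90, launch must come after December 2014. The two conditions do not overlap.

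**Launch 1 October 2014.**
- Day 90 on or after launch: births 3 July-30 September, 29 + 31 + 30 = 90 dates; 90/183 = 49%.
- Whole 60-90 day window on or after launch: births 2 August-30 September, 30 + 30 = 60 dates; 60/183 = 33%.

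**Launch 1 January 2015.**
- No baseline date is affected.
- Endline pregnancy exposure: 31 days (1.0 month) for a birth on 1 February, 211 days (6.9 months) for a birth on 31 July. Only about 50% of endline birth dates have 4 months or more.
- A typical first antenatal visit falls 9 − 5.4 = 3.6 months (about 110 days) before delivery. Births up to 20 April 2015 would have had it before launch: 28 + 31 + 20 = 79 dates; 79/181 = 44%.

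**Across the range.**

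| Launch | Baseline: day 90 on or after launch | Baseline: whole 60-90 day window on or after launch | Endline pregnancy exposure (months) |
|---|---|---|---|
| 1 Oct 2014 | 49% | 33% | 4.0 to full pregnancy |
| 1 Nov 2014 | 32% | 16% | 3.0 to about 8.9 |
| 1 Dec 2014 | 16% | 0% | 2.0 to 8.0 |
| 1 Jan 2015 | 0% | 0% | 1.0 to 6.9 |

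The November and December rows break both statements, each in part.

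**Sections 6.3 and 6.4.** Nine months back from the opening of endline assessment (1 May 2015) is about 1 August 2014; nine months back from its close (31 October 2015) is about 1 February 2015. A launch on 1 October 2014 would put the close at about 13 months. A minimum of 6 intervention months fits many dates. Neither section settles the launch.

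**The case against.** **Figure 4 may show the launch date.** It is the cohort timeline and is not reproduced in the text at hand, so the protocol cannot be faulted for omitting the date. This stands. It does not remove the contradiction, because no date in the figure could make both sentences true.

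**Unexposed may mean unexposed in pregnancy.** Baseline births end on 30 September 2014, the day before the inferred October launch, so this may be what was intended. The text does not say so. It would not protect outcomes measured at 60-90 days postpartum, and Section 7.1 itself counts the postpartum period as exposure for endline women.

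**Assessed after launch is not the same as exposed.** This stands. Only intervention-arm women can be exposed, contact is monthly, and the card is collected after infant testing at 6-8 weeks, so women later in the postpartum period may never receive it. The 49% is a ceiling on possible exposure for that launch date.

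**The 9 months in Section 6.3 may favour a launch around February 2015.** Counted from the close of endline assessment, it does. The baseline would then be clean and the 4-9 months would be the misstatement. This is suggestive only, since counting from the opening points to August 2014.

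**Stronger readings that the protocol does not support.** A reader might infer that the analysis would recover only 6.6-8.7 of the planned 13 points, from 13 × (1 − 0.49) and 13 × (1 − 0.33). That assumes postpartum contact alone carries the whole effect from launch day. The 13 points in Section 6.4 is the planned difference for the intervention as a whole, and nothing says what share comes from postpartum contact. A reader might also infer that ART timing could not respond under a January launch. Women past their first antenatal visit but not yet on ART could still respond, and 5.4 months is a national average, so dilution is the most that can be said.

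**Conclusion.** Section 7.1 is internally inconsistent, whatever the launch date. The consequence depends on which statement gives way.

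- **If launch was about 1 October 2014,** up to 49% of intervention-arm baseline birth dates could carry some exposure, and 33% have the whole retention window after launch. If the intervention helps postpartum women, the difference-in-differences for retention and adherence is biased toward the null. The direction follows from the design; the size does not follow from the documents.
- **If launch was about 1 January 2015,** the baseline is sound, the 4-9 months should read about 1.0-6.9, and the ART-timing effect is diluted, with about 44% of endline births having a typical first antenatal visit before launch.
- **If launch fell between,** both problems occur in smaller measure.

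The percentages assume uniform births. The 44% also applies the average first-visit time to every woman.

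**What to change.** Anchor both cohorts in Section 7.1 to the actual launch date, by one rule applied identically in both arms.

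- **Launch before the end of December 2014:** restrict the baseline to births whose day 90 precedes launch. For 1 October 2014 that means births up to 2 July 2014, either by moving the six-month window earlier (3 January-2 July 2014) or by truncating the present one at 2 July. Where launch is later than about 1 October, correct the 4-9 months as well.
- **Launch after December 2014:** keep the baseline dates and correct the 4-9 months to the true range.
- **In either case:** reconcile the 9 months in Section 6.3 and the 6 intervention months in Section 6.4 with that date.
- **ART timing under a late launch:** report the effect as diluted, or add a sensitivity analysis limited by birth date alone to later endline births. Do not restrict to women not yet on ART at launch: that would select late initiators at endline with no matching restriction at baseline.

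**Cost.** Protocol wording and a changed date filter on records that are abstracted retrospectively anyway. A moved baseline lies closer to the Option B+ roll-out, which Section 2 dates from September 2013: a birth on 3 January 2014 has a typical first antenatal visit in mid-September 2013. Facility roll-out dates are not given, so balance between arms on this cannot be assumed. A truncated baseline is smaller: 1 April-2 July is 93 of 183 dates, about half.

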Increasing retention in the PMTCT cascade is particularly critical in high-burden, priority countries like Tanzania, where 6.2% of women aged 15-49 are HIV-positive and nearly one quarter of pregnant women living with HIV do not receive ARVs/ART for PMTCT. Notably, in Tanzania, achievements in PMTCT could have important impacts on the national epidemic, as 1 out of every 5 new HIV infections are due to mother-to-child transmission – an estimated 36,225 infections per year. In September 2013, Tanzania began rolling out 'Option B+' to all 6,270 reproductive and child health (RCH) facilities, the PMTCT strategy whereby HIV-infected pregnant women receive ART throughout their lives regardless of clinical stage. By simplifying service delivery, drug regimen, and reducing the number of steps that mothers need to negotiate (such as CD4 testing), Option B+ is expected to improve retention in the PMTCT cascade. However, the postulated benefits of Option B+ are predicated on mothers remaining on lifelong ART, starting at the time of HIV diagnosis. Thus, a critical unresolved issue is whether *asymptomatic* women who learn their HIV status during pregnancy will initiate and adhere to ART under Option B+.

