## 3. BACKGROUND AND REVIEW OF LITERATURE

### *PMTCT & Option B+*

Malawi was the first to implement the Option B+ strategy, and the initial monitoring and evaluation data were encouraging: Option B+ dramatically increased ART coverage among HIV-infected pregnant women, among whom 77% continued to receive treatment at 12 months, comparable to 80% of adults in the national program. However, more recent cohort data paint a decidedly less optimistic picture, as Option B+ patients who started ART during pregnancy were five times more likely to never return after their initial clinic visit compared to women who started ART because they were treatment eligible. In the same analysis, pregnant women who started ART on the day of HIV diagnosis had the highest loss to follow-up rates. Furthermore, a meta-analysis of 51 studies, including over 20,000 HIV-infected pregnant and postpartum women, found that adherence (80% or higher) was a modest 53% in the postpartum period compared to 76% antepartum. Together, these data highlight the central challenge for eMTCT

and keeping women alive: preventing attrition from the treatment and care cascade and achieving high levels of adherence to ART.

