## 6. DESCRIPTION OF THE EVALUATION

### 6.1. Evaluation Questions

In tandem with the program, we will conduct an impact evaluation to measure the effectiveness of the program. The primary objectives of the evaluation will be to answer the following questions:

1. What is the impact of integrating community-based MNCH and PMTCT services using CHWs in Shinyanga, Tanzania on:
  - a. The timing of ART initiation among HIV-infected pregnant and postpartum women;

- b. Retention of HIV-infected women in care 90 days postpartum; and
  - c. Adherence to ART at 90 days postpartum.
2. Is the impact of integrating community-based MNCH and PMTCT services on retention in care and adherence greater among women who had more contact with CHWs?
3. Is integration of community-based MNCH and PMTCT services acceptable and feasible for CHW, health facility staff, and pregnant and postpartum women, and are there potential spillover benefits on other maternal health outcomes?

[figure not shown]

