## 6. 2 Impact and Process Indicators

### Impact Outcomes:

1. Timing of ART initiation: The timing of ART initiation among HIV-infected pregnant women according to gestational age (The number weeks since the first day of the last menstrual period (LMP)). We hypothesize that women in intervention communities will initiate ART earlier than women in comparison communities.
2. Retention in care: Whether an HIV-infected pregnant or postpartum woman on ART is still in care 90 days postpartum (binary 1/0). In Tanzania, postpartum women on ART are typically scheduled for clinical monitoring for their own health at 7, 28, and 42 days (6

week postnatal visit) and then every 30 days thereafter until transfer to the HIV clinic at 18 months. We define retention as a woman who attended her scheduled visit between 60-90 days postpartum.

3. Adherence: We will measure adherence with the medication possession ratio (MPR), the proportion of days when ART was prescribed and an individual is in possession of ART (determined with pharmacy dispensing data). MPR is associated with short-term virologic outcomes. We will determine the proportion of women with MPR  $\geq 95\%$  at 90 days postpartum (binary 1/0).

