## 7.2. Data Sources

Data will be abstracted from the following sources, using the woman's clinic identification number (clinic ID) as the unique code to link across data sources:

- **CHW logs:** CHWs maintain standardized logs of pregnant and postpartum women in their catchment area. At the start of the study, we will modify the log form to include women's clinic ID. We will retrospectively abstract the clinic ID along with demographic data about both HIV-infected and uninfected women in the baseline or endline cohorts, as CHW in comparison villages may not know women's HIV serostatus. Note that this is a significant strength of our study, as we will have a community-based measure of pregnant women, including women who do not utilize RCH services.
- **ANC register:** Contains information about all women who booked for ANC, including number of visits, HIV testing results, health facility delivery, and attendance at the postnatal visit. We will abstract these data for each woman in the baseline or endline cohort and match their health information with CHW log information.
- **ART register:** Contains information about HIV-infected pregnant or postpartum women who are initiated on ART at RCH clinics. For all HIV-infected women in the baseline or endline cohorts, we will match them to the ART register to determine whether they initiated ART and attended visits.
- **CTC2 Cards:** Contains individual medical record data for HIV-infected women. We will abstract data from these cards as needed, to supplement data in the ART register.
- **Pharmacy logbook:** Contains ART pick-up dates and quantity for HIV-infected women.

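### The cohorts mix women already on ART with women starting it in pregnancy, while the power assumption and the main register describe starters, so ART status at LMP should be recorded and used

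*Protocol*

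**What the plan says.** Protocol 7.1 sets two cohorts. The first is "The baseline cohort will include HIV-infected women who were 90 days postpartum between July 1 and December 31, 2014", and the second is "The endline cohort will include HIV-infected women who are 90 days postpartum between May 1 and October 31, 2015". Neither carries a criterion on ART status or start date, and none is added in 6.2, 7.2, 7.3 or Table 1.

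Several parts of the protocol have women starting ART in view:

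- The problem statement (section 2) names as unresolved whether asymptomatic "women who learn their HIV status during pregnancy will initiate and adhere to ART under Option B" (that is, Option B+).
- Section 6.4 derives the control rate from a preliminary analysis of women who initiated ART, and argues feasibility from about 11 initiations per month at many clinics.
- Section 7.1 defends the length of exposure by the first ANC visit as the first chance to start ART.
- The timing outcome in 6.2 is "The timing of ART initiation among HIV-infected pregnant women according to gestational age".

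Other parts are general. Question 1b in 6.1 is "Retention of HIV-infected women in care 90 days postpartum", and Table 1 uses all HIV-infected pregnant women as the retention denominator.

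On data, 7.2 describes the ART register thus: "Contains information about HIV-infected pregnant or postpartum women who are initiated on ART at RCH clinics". For every HIV-infected cohort woman it then says "we will match them to the ART register to determine whether they initiated ART and attended visits". CTC2 cards supplement this register only where needed. Table 1 lists the ART register, CTC2 cards and CHW register as sources for retention.

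**The concern.** A woman on ART before conception differs from a starter in two ways that matter here.

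First, the 67% and the planned 13-point gain rest on experience in initiators. If established patients are better retained and have less room to improve, mixing them in shrinks the difference on the powered outcome.

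Second, a register described by where women were initiated may not hold a woman who started earlier or elsewhere. The protocol gives no rule for a cohort woman who cannot be matched to it. With all HIV-infected women in the denominator, she could be counted as not initiated and not retained even if she is well engaged in care.

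The timing outcome is affected too, since gestational age at initiation has no defined value for a woman treated before her LMP.

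**Working it through.** **Inputs from Protocol 6.4:** retention 0.67 against 0.80; ICC 0.05; 15 communities per arm; 36 women per community; 80% power. Alpha is not stated, and 0.05 two-sided is assumed.

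**Reproducing the plan's figure.** The two-proportion formula with continuity correction gives 195 per arm. The design effect is 1 + (36 − 1) × 0.05 = 2.75. Then 195 × 2.75 = 536.25, rounded up to 537 per arm, which is the protocol's number. Without the correction, 180 × 2.75 = 495, so the plan used the correction.

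**Base power.** Effective n per arm = 15 × 36 / 2.75 = 540 / 2.75 = 196.4. Power = Φ{[Δ − 1.96 √(2p̄(1 − p̄)/n)] / √[(p₁(1 − p₁) + p₂(1 − p₂))/n]}. With Δ = 0.13 this is 0.83. Subtracting 1/n from Δ as a continuity correction gives 0.80.

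**Illustration A: dilution only.** Assume a share s is on ART before LMP, with 90% retention in both arms and no intervention effect. Neither s, the 90% nor the zero effect is in the protocol. Control = 0.67(1 − s) + 0.90s; intervention = 0.80(1 − s) + 0.90s; difference = 0.13(1 − s).

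| s | Control | Intervention | Difference (points) | Power, no correction | Power, corrected |
|---|---|---|---|---|---|
| 0 | 0.670 | 0.800 | 13.0 | 0.83 | 0.80 |
| 10% | 0.693 | 0.810 | 11.7 | 0.77 | 0.73 |
| 20% | 0.716 | 0.820 | 10.4 | 0.69 | 0.64 |
| 30% | 0.739 | 0.830 | 9.1 | 0.59 | 0.54 |

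**Illustration B: established women also coded as not retained.** This is the worst case, and no text prescribes it. Control retention reads 0.67(1 − s) = 0.603, 0.536 and 0.469. The differences are as in A, and power (no correction) is 0.69, 0.55 and 0.44. If only half are so coded, power at s = 20% is 0.60.

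**Illustration C: no harm.** If established women have the same 67% to 80% response and are fully traced, the difference stays at 13 points and power at 0.83.

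**Looking at starters within a mixed sample of 36.** Cluster size becomes 36(1 − s) = 32.4, 28.8 and 25.2, and power for 67% against 80% (no correction) is 0.82, 0.80 and 0.78. Under the assumptions of A, the smaller stratum loses less than dilution does. At 11 initiations per month, a six-month cohort has 11 × 6 = 66 starters in such clinics, above 36.

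**Is ART status at LMP fixed before exposure?** Endline births run from 1 February to 31 July 2015, so LMPs (280 days earlier) run from about late April to late October 2014. The 4 to 9 months of antenatal exposure stated in 7.1 put the start of the intervention at about October 2014. Status at LMP is therefore essentially settled beforehand, and splitting on it introduces no appreciable selection.

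**The case against.** Four stronger readings are tempting, and the protocol does not support them.

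- *The trial is about new starters, so the cohort is the wrong population.* The problem statement leans that way, but questions 1b and 1c, the retention definition and Table 1 refer to HIV-infected women, or women on ART, in general. The intervention (section 5) counsels all women on ART and traces anyone who misses appointments. Including established patients fits those questions; restricting to starters would change them.
- *Unmatched women are scored as lost.* No such rule is written. Table 1 gives two further retention sources, and 7.4 adds back-checks against CHW logs. Section 6.2 describes postpartum women on ART as typically monitored on a set schedule until transfer to the HIV clinic at 18 months, and nothing shows established patients being followed elsewhere at 60 to 90 days. What stands is that the look-up is discretionary and the register's description does not cover them.
- *The protocol shows that established patients are more stable.* The statement in section 3 that "Option B+ patients who started ART during pregnancy were five times more likely to never return after their initial clinic visit" compares them with women who started ART because they were eligible. Both groups are starters, so it says nothing about women treated before conception.
- *The two cohorts differ in composition, so the comparison is biased.* The share already on ART may rise as Option B+ matures, but 7.4 plans difference-in-differences, which absorbs a shift common to both arms. Under simple randomization of 30 communities the shift may not be exactly equal, but that is a matter of chance imbalance.

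Stratification might also be specified in an analysis plan not seen here. The power assumption, the cohort definition and the source rules, however, are fixed in the protocol.

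**Conclusion.** The point holds as a mismatch with a possible cost. The cohorts pool two groups of women, the power assumption is drawn from one of them, and the main data source is described in terms of that same group. The size is conditional. Shares of 10 to 30% would take the difference to 11.7 to 9.1 points and power to 0.77 to 0.59 (no continuity correction), but only if established women have about 90% retention and no benefit. If they respond alike and are fully traced, the cost is zero. Misclassification would lower power further, and if similar in both arms would mainly dilute the effect. A modest change is worth making because it improves precision and reduces outcome error at little cost.

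**What to change.** 1. Keep all HIV-infected women as the population for questions 1b and 1c.
2. From the ART start date already abstracted for the timing outcome (ART register and CTC2 card in Table 1), classify every woman as on ART before LMP or not, in both arms and both cohorts. This also shows for whom the timing outcome is defined.
3. Stratify or adjust the retention and adherence analyses by this status, and report the effect in women not on ART at LMP alongside the overall effect. Women who never start remain in that group.
4. Before coding any woman missing from the RCH ART register as not initiated or not retained, check her CTC2 card and the other retention sources in Table 1, in both arms and both cohorts. Do not code documented ART care elsewhere as loss.

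The cost is some extra CTC2 look-ups and a few lines of protocol text. Precision will be lower in the new-starter stratum, and the stated 80% power should not be claimed for it unless 36 such women per community are reached.
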